**4.6. Study Withdrawal and Stopping Criteria**

The parents of the participating child are free to withdraw their child from the study at any time without needing to provide a reason. The protocol will also be terminated if a socio-medical imperative arises during the study that requires it to be stopped. In such a situation, the final assessment will be performed at the time of study discontinuation, if possible. The study will be stopped after the last visit of the last enrolled patient. The sponsor can decide to terminate the study prematurely. The sponsor must then inform the CPP within 15 days and state the reasons for this decision. At the end of the study, the sponsor will inform the CPP and the investigating centers within 90 days. In the event of premature study termination, the investigators must promptly inform the participating patients and ensure they receive appropriate follow-up care.

**4.7. Duration of the Research and Compensation**

- **Duration of patient participation in the protocol:** 12 months
- **Duration of the inclusion period:** 30 months
- **Anticipated duration of the research (inclusion + analysis):** 54 months
- No compensation is planned.

**4.8. Exclusion and Exclusivity Period**

- **Exclusion period:** For the entire duration of the study, the participant in this study cannot participate in any other research involving human subjects.
- **Exclusivity:** The participant cannot take part in any other interventional research during this study.

**5. Benefits and Risks**

**5.1. Benefits for the Participant**

All children with CP participating in this study will benefit from RAIT rehabilitation for either 9 or 12 months. If RAIT shows the same effects as in our previous study on children aged 5 to 12, the expected direct benefits are better balance control during sitting and standing and improved walking dynamics (trunk decelerations and foot dynamics). Furthermore, in cases of upper limb motor abnormalities, improved use of the upper limb and hand (associated extension of the elbow, wrist, and fingers; manual dexterity) is also expected, based on unpublished clinical experience. The physical therapists and the patients' parents will be able to continue this care even after the study ends.

**5.2. Risks and Constraints for the Participant**

There are no major risks for the participant concerning the treatments and assessments performed. The postural activities, in which muscles and tendons are stretched, could initially be painful. However, any muscle and tendon pain, should it occur, would be mild and temporary because the stretching of muscles and tendons will be progressive, especially since the child performs the postural activities themselves.

The constraints related to the study are quite significant. The RAIT postural activities or, where applicable, a suitable selection of exercises related to usual rehabilitation prescribed by the physical therapist, must be performed regularly, every day, for at least 15 to 30 minutes (in one or more sessions). The home sessions are complementary to those performed with the physical therapist. An adult will need to be present during home sessions to supervise the child. The postural activities or usual rehabilitation exercises performed by the child at home will be recorded in a logbook so that their progress can be monitored by the physical therapist and the CMPRE team. There will be a total of 4 sessions at the CMPRE: at the start of the study and then at 3, 6, and 12 months. Each session will last several hours (2 to 4 hours) spread over one day and will include the motor function assessment and a medical consultation to review the postural activities. A member of the CMPRE team will contact the parents via teleconsultation once or twice between each motor function assessment at the CMPRE to answer their questions.

**6. Safety Evaluation**

**6.1. Adverse Events**

**6.1.1. Definitions**

- **Adverse Event:** Any harmful occurrence in a person participating in research involving human subjects, whether or not it is related to the research or the product being studied.
- **Adverse Effect:** An adverse effect of a research study corresponds to any adverse event caused by the research.
- **New Event/Finding:** Any new data that could lead to a re-evaluation of the benefit-risk ratio of the research or the product under investigation, to changes in the use of this product, in the conduct of the research, or in the research documents, or to the suspension, interruption, or modification of the research protocol or similar research.

**6.1.2. Serious Adverse Event(s)**

In this study, regardless of the intensity or duration of the treatment, any adverse event or effect will be considered serious (SAE) if it:

- Results in death.
- Is life-threatening to the participant.
- Requires hospitalization or prolongation of existing hospitalization.
- Results in persistent or significant disability or incapacity.
- Results in a congenital anomaly or birth defect.
- Constitutes a medically significant situation.

In this protocol, the following will not be considered serious (SAE):

- An event leading to a temporary visit to a hospital consultation, an emergency room, or a day hospital.
- Hospitalizations for elective procedures not associated with a worsening of the clinical condition and not related to the objective of the clinical study, occurring during the clinical study (e.g., cosmetic surgery).
- Hospitalizations (more than one night) or extensions of hospitalization for the following reasons : planned hospitalizations for routine interventions or treatments as part of a pre-defined monitoring or therapy program ; hospitalizations for investigations not related to a change in the participant's condition ; or hospitalization for convenience or social reasons.

**6.2. Procedures to Follow**

All adverse events occurring during the study, whether observed by the physicians or reported by the patients and regardless of the suspected causality, must be recorded in the case report form and followed up appropriately. For each adverse event, the following should be reported whenever possible:

- Its description or diagnosis.
- Its duration (start and end dates).
- Its severity (mild, moderate, severe).
- Its relationship to the investigational product (related/unrelated).
- The measure(s) taken and the outcome.

**Severity Scale for Adverse Events**:

|  |  |  |
| --- | --- | --- |
| **1** | **Mild** | Symptom(s) barely noticeable to the patient or causing no discomfort. The AE has no behavioral or functional effect. Treatment of the symptom(s) is generally not necessary. |
| **2** | **Moderate** | Symptom(s) of sufficient severity to inconvenience the patient. Daily activity is altered. Treatment of the symptoms may be necessary. |
| **3** | **Severe** | Symptom(s) of sufficient severity to seriously inconvenience the patient. The severity may lead to treatment discontinuation. Treatment of the symptoms may be necessary. |

**Relationship between Adverse Events and the Measurement Procedure**:

|  |  |  |
| --- | --- | --- |
| **0** | **Unrelated** | The chronological relationship between the occurrence of the clinical event and the performance of the measurement makes any causal link improbable, or other medications, therapeutic procedures, or underlying conditions provide a sufficient explanation for the observed event. |
| **1** | **Related** | The chronological relationship between the occurrence of the clinical event and the performance of the measurement makes a causal link possible. Furthermore, other medications, therapeutic procedures, or underlying conditions do not provide a sufficient explanation for the observed event. |

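### The only causality scale for adverse events refers to the measurement procedure, while the rest of the safety section asks about the product or the research

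*Protocol*

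**What the plan says.** Protocol section 6.2 requires every adverse event to be recorded whatever its suspected cause, with its description, dates, severity, action taken and outcome. It also asks for "Its relationship to the investigational product (related/unrelated").

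The table that defines the two answers comes later in the same section, under the heading "Relationship between Adverse Events and the Measurement Procedure". Code 0 (unrelated) applies if either of two tests is met:

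- The timing test is worded "The chronological relationship between the occurrence of the clinical event and the performance of the measurement makes any causal link improbable".
- The alternative-explanation test, which suffices on its own, is worded "other medications, therapeutic procedures, or underlying conditions provide a sufficient explanation for the observed event".

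Code 1 (related) needs two things together: that the timing relative to "the performance of the measurement makes a causal link possible", and that no such alternative explanation is sufficient.

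The other safety passages use a wider object. Section 6.1.1 states that "An adverse effect of a research study corresponds to any adverse event caused by the research". Section 6.2.1 has the investigator report every serious adverse event whether or not it is thought to be related to the research or the study product, and has the sponsor assess serious events against the study product or the research.

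On expected harms, section 5.2 says of the rehabilitation: "The postural activities, in which muscles and tendons are stretched, could initially be painful". It expects such pain to be mild and temporary.

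**The concern.** The investigator is asked a question about the intervention but is given answer categories that are defined for the assessments. In this trial the two are quite different exposures. The assessments are four visits over 12 months. The exercises "must be performed regularly, every day, for at least 15 to 30 minutes", in addition to the sessions with the physical therapist. The physical harm that the protocol foresees comes from the exercises.

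What is at stake is attribution. If some investigators apply the table and others apply the wording of the reporting list, the same event can be coded 0 by one and 1 by another. If the table is followed consistently, pain caused by RAIT is coded as unrelated. In either case the count of related non-serious events, in a planned sample of 32 children with CP aged 18 months to 5 years and 6 months, would not be a dependable description of how RAIT is tolerated.

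**Working it through.** No arithmetic applies, so the check sets the passages side by side and then applies the table to the foreseen event.

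**Step 1. What is causality judged against?**

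| Place in the protocol | Object of the causal judgement |
| --- | --- |
| 6.1.1, definition of adverse effect | The research |
| 6.2, list of items to report | The investigational product |
| 6.2, table of relationship categories | The measurement only |
| 6.2.1, investigator's role (serious events) | The research or the study product |
| 6.2.1, sponsor's role (serious events) | The study product or the research |

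Four of the five places name the research or the product. The one that differs is the only one that defines the categories. The study rehabilitation is not named in the heading of that table or in either row.

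**Step 2. Apply the table to the foreseen event.** Take muscle pain that starts during a home RAIT session midway between two assessments.

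- *First route to code 0, timing.* The last measurement was weeks earlier and the next is weeks away. A causal link to a measurement is improbable, so the event is unrelated.
- *Second route to code 0, alternative explanation.* RAIT is a therapeutic procedure and it explains the pain sufficiently, so the event is again unrelated. The object being judged is the measurement, so RAIT counts among the other explanations. Identifying RAIT as the cause therefore supports the answer unrelated.
- *Code 1.* This needs both a possible link to a measurement and the absence of another sufficient explanation. The event fails both conditions.

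**Step 3. Move the event close to a visit.** Suppose the same pain occurs the day after an assessment. Timing may now allow a link to the measurement, but if RAIT explains the pain the second route still gives code 0. The alternative-explanation clause would thus remain a problem even if the timing test were read generously.

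**Step 4. Is the gap filled elsewhere?** The severity table in section 6.2 grades intensity, and its top grade mentions that treatment may be discontinued, so the section is meant to cover the treatment. It does not address cause. Section 6.2.1 gives the sponsor a causality assessment but no scale, and it covers serious events only. No other definition of related and unrelated appears in the protocol.

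**The case against.** The strongest reply is that the protocol does not force the wrong answer. The reporting list in section 6.2 asks about the investigational product, and section 6.1.1 defines an adverse effect by reference to the research. An investigator who follows those two places can record RAIT pain as related. Since four of the five places point to the research or the product, the table looks like a wording slip rather than a decision to exclude RAIT. All of this stands. The point is therefore an internal contradiction, and miscoding is a risk of following the table, not a certainty.

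It is also fair to say that the consequences are bounded. Every event is recorded with enough detail for its attribution to be revisited, no safety endpoint is listed in sections 2.2 or 2.4, and the foreseen pain is described as mild and temporary. These facts limit the importance of the point. They do not remove it, because non-serious events, where mild pain would most likely fall, receive no separate causality assessment by the sponsor in section 6.2.1.

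Three stronger readings are tempting, and the documents do not support them:

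- *RAIT would be reported as free of related events by construction.* That holds only if everyone follows the table and nobody follows the reporting list.
- *The sponsor's review of serious events would start from a wrong classification.* All serious events are reported regardless of suspected cause, and the sponsor assesses them against the study product or the research. Neither passage refers to the table, and the reporting form is not shown.
- *Only about 1% of participation days (4/365 = 1.1%) could yield a related event.* This assumes that an event must fall on the day of an assessment. The table sets no such window, and a share of days is not a share of events.

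**Conclusion.** The point holds as an internal contradiction with a practical consequence. The protocol's only definition of related and unrelated is tied to the measurements, and applied literally it codes the harm foreseen from RAIT as unrelated by two separate routes. Related non-serious events could therefore be under-reported or coded inconsistently.

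The size cannot be expressed as a number, because the documents give neither an expected event rate nor any indication of which wording investigators would follow. What is affected is the attribution of non-serious events. The recording of events, the reporting of serious events and the efficacy analysis are not affected.

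The conclusion rests on two assumptions: that the investigational product in section 6.2 means the study rehabilitation, and that the table is meant to define the answers to that item, since both use the same two categories and no other definition is given. The case report form is not available and might already word the item differently. Even so, the protocol text should be made consistent.

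**What to change.** Revise the relationship table in section 6.2 as follows.

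- **Heading:** refer to the study rehabilitation and the study assessments, not to the measurement procedure alone.
- **Both rows:** replace the reference to the measurement by a reference to the study rehabilitation (RAIT or RH, supervised or at home) or a study assessment. RH belongs here because section 4.2 also sets a daily home component for the RH period.
- **Alternative-explanation clause, both rows:** limit it to therapeutic procedures other than the study rehabilitation.

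Then check that sections 6.1.1, 6.2 and 6.2.1 use the same object throughout.

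Recording attribution to the rehabilitation and to the assessments as two separate items would be informative, as would a tabulation by group for M0 to M3, the only interval in which one group receives RH. Both are optional, and the tabulation can be left to the statistical analysis plan.

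The cost is the rewording of one table, with a matching check of the case report form. The design, the sample size and the clinical procedures do not change.

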**6.2.1. Procedures to Follow in Case of a Serious Adverse Event**

**Investigator's Role(s)**

To ensure patient safety, any serious adverse event, whether or not the investigator suspects it to be related to the research or the study product, must be reported using the serious adverse event reporting form and sent by email to the Institut Régional de Médecine Physique et de Réadaptation de Nancy ([contact]), an establishment of UGECAM du Nord-Est, without delay from the day the investigator becomes aware of it. The "Serious Adverse Event Reporting Form" found in the case report form must be completed, signed, and sent, possibly electronically, to the coordinating investigator, [name] ([contact]), and to the sponsor's representative, [name] ([contact]). The investigator follows up on participants who have experienced a serious adverse event until the event is considered resolved.

**Sponsor's Role**

The Institut Régional de Réadaptation de Nancy will :

- Review the serious adverse event forms submitted by the investigator.
- Assess the possible relationship with the study product or research and its expectedness.
- Request additional information from the investigator if necessary.
- Complete the section reserved for the sponsor on the serious adverse event forms.
- In accordance with Article R1123-59 of the Public Health Code, the sponsor will promptly inform the competent authority and the Committee for the Protection of Persons of any new findings and, if applicable, of the measures taken.

**7. Data Management**

**7.1. Right of Access to Data**

The investigator agrees to allow free access to study data to the sponsor, monitors, auditors, or representatives of Health Authorities. At the end of the study, if the volunteer wishes, they may be informed of the overall results of the research. The participant must make a written request to the coordinator.

**7.2. Source Data**

Source documents are defined as any original document or object that can prove the existence or accuracy of a piece of data or a fact recorded during the clinical trial. They include original documents, data, and records from which the study data concerning the subject are transcribed into the case report form. This includes, among other things, the medical record, examination reports and results, questionnaires, and medical correspondence.

**7.3. Participant Anonymity**

The anonymity of participants will be ensured by assigning them a unique alphanumeric reference, for example, FLA-001 for the first participant. This reference will be used to name the files containing the data to be analyzed and to perform calculations and statistical studies. Video and photo recordings may be taken, subject to the participant's consent. The participant's anonymity will be ensured by masking their face and any distinguishing features.

**7.4. Confidentiality**

In accordance with the provisions of Article R. 5120 of the Public Health Code, the investigator and any person called upon to collaborate in the trials are bound by professional secrecy.

**7.5. Archiving**

At the end of the study, all study-related documents (including a copy of the case report forms) will be archived at the study sites or in a centralized archive. All study-related documents must be kept for 15 years after the end of the study.

**7.6. Rules for Publication of the Final Report**

This study will lead to publications and the writing of master's theses and/or dissertations. A summary of this final report will be sent to the CPP within 12 months following the end of the study.

**8. Quality Assurance**

**8.1. Investigator's Commitment - Good Clinical Practices**

The investigator undertakes to respect the protocol and to apply it taking into account good clinical practices. The investigator agrees to allow free access to study data to the sponsor, monitors, auditors, or representatives of Health Authorities.

**8.2. Data Quality Control**

Once the data are entered, data checks (consistency and missing data checks) will be carried out regularly for the clinical data. Missing or inconsistent data will be sent back to the investigators for additional information and verification.

**8.3. Audit and Inspection**

The investigators and the sponsor agree to comply with the requirements of these assessments, should they be carried out.

**9. Study Organization**

**9.1. Scientific Committee**

The scientific committee is led by [name]. Its objectives are to define the study's objective, write the protocol and the case report form, and select the centers. It will also ensure the smooth running of the study from a scientific and logistical standpoint, resolve any difficulties encountered, and make all decisions concerning the study (amendments, decisions on its premature termination or extension, re-evaluation of the study's sample size, etc.).

**10. Ethical and Regulatory Considerations**

**10.1. Research Site Authorization**

The IRR is a healthcare facility where the procedures performed in this research are those usually practiced as part of its activity.

**10.2. Ethical Conduct of the Study**

The planning and conduct of this study are governed by French and European laws (in particular, Decree No. 2016-1537 (Jardé Law) of November 16, 2016). The study will be conducted in accordance with the ethical principles of the Declaration of Helsinki and the recommendations of Good Clinical Practices.

**10.3. Committee for the Protection of Persons (CPP)**

The trial cannot begin without having received authorization from the CPP. The protocol will start upon receipt of a favorable opinion from the CPP. Any substantial modifications must be submitted as an amendment to the protocol and receive approval from the CPP before being implemented.

**10.4. Investigator's Responsibilities**

The investigator undertakes to ensure that this study is conducted in compliance with Law No. 2004-806 of August 9, 2004, on public health policy and its implementing decrees, the Declaration of Helsinki, and Good Clinical Practices. The investigator will inform volunteers about the study's objectives and constraints, and their right to refuse to participate or to withdraw at any time. The investigator will obtain written consent after ensuring the volunteer has understood the implications of participation.

**10.5. Sponsor's Responsibilities**

In accordance with the law, the sponsor commits to:

- **Insurance:** The sponsor has taken out insurance for the entire duration of the study to cover its own civil liability as well as that of any intervener involved in the trial.
- **Committee for the Protection of Persons:** The sponsor will seek the opinion of a CPP. The research can only be implemented after a favorable opinion from the CPP.
- **National Commission on Informatics and Liberty (CNIL):** This study falls under the MR-001 methodology. The Sponsor sent a declaration of conformity to the CNIL on 25/01/2021 under the number 2220869.

